#### Preparation of the intervention

Based on a systematic literature research and a workshop for experts and representatives of the older adults in Denmark, a tool to be used in the rehabilitation process and the dialog between the Case Manager/RD and the older adults was developed. This tool will be new and is not a validated standardized tool. Both Goal Attainment Scaling (GAS) and “A common terminology for community aged care in Denmark” (FSIII) will be used in this tool. GAS offers many potential advantages as an outcome measure for rehabilitation, and moreover there is also evidence that GAS has positive therapeutic value in encouraging the participants to reach their goals [22]. FSIII is a generic process model using the same concept and the same way of describing the reasons for care planning and interventions in rehabilitation programs in order to efficiency improvement of the communication [23]. The tool includes the following focusses of meals:manage shopping (i.e. help to plan the shopping, grocery shopping),increase cooking abilities (e.g. semi-prepared meals-on-wheels, assistance to cook at home),focus on social aspects of meals (e.g. eating together with family, buddies/volunteers), andimprove ability to eat independently (e.g. in relation to dysphagia).

The intervention consists of two parts targeted at individual participant level:First part of the intervention: Education and training

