In the present study, goals will be short-term (i.e. realistic to reach within the intervention period), and a maximum of three goals will be selected for change.

Thus, the Case Managers will encourage participants to involve in these activities.

When *implementing* the activities in relation to meals the Care Manager/RD will plan the intervention interdisciplinary with other professionals within The City of Odense e.g. Occupational Therapist, Physiotherapist, Health Care and Kitchen Staff. A period of eight weeks is chosen for the rehabilitation program in order to get a realistic comparison. This is the minimum amount of time for a Danish municipality rehabilitation program [21]. The intervention is individual and will consist of a minimum of three contacts to the Case Manager/RD in order to *monitor* and *reassess*. After completion of the rehabilitations program a final evaluation will be made.

The participants in the control group will receive usual care in relation to meals; this includes a number (one to seven) hot meals-on-wheels arriving one to three times per week, along with usual support at home.

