### Outcomes

The outcome assessments, conducted in the participants homes by Research Assistants (RA) and Case Managers/RD’s will occur at inclusion (Baseline, *t* = 0) and at the end of the intervention period (Follow-up, *t* = 2). At the beginning of second part of the intervention some outcome assessments will also be conducted in only the Intervention cluster (In between, *t* = 1). It is, however, not obtained by the same person at baseline, in between, and follow-up for practical reasons. However, all will receive the same training in the methods on obtaining outcome assessments by RA ([name]) or RA ([name]). Due to the design of the study it is not possible to blind neither the RA’s nor the Case Managers/RD’s. An overview of the outcome measurements is presented in Table 1 and described in detail below.

**Table 1 Tab1:** Data collection 2 Content in fridge (sufficient, insufficient, empty)

Measure	Time of data collection		
	Baseline *T* = 0	In between *T* = 1	Follow-up *T* = 2
Quality of life by EQ-5D-3 L	X	X	X
Height, meter	X	X	X
Weight, kg	X	X	X
BMI, (kg*kg/m2)	X	X	X
Muscle strength - Chair stand^1^	X	X	X
Satisfaction with food-related life	X	X	X
UCLA Loneliness Scale	X		X
The Short Warwich-Edinburgh Mental Well-being Scale	X		X
General Self Efficacy Scale	X		X
Refrigerator content^2^	X		X
Sociodemographic	X		
Meals-on-wheels (days/w)	X		

^1^Rise from a chair without using the arms in 30 s

^2^Content in fridge (sufficient, insufficient, empty)

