The satisfaction with food-related life will be measured by the Satisfaction with Food-related Life (SWFL) scale (at *t* = 0, *t* = 1, *t* = 2). The SWFL, consists of 5 items grouped into a single dimension (e.g. Food 1: Food and meals are positive elements; Food 2: I am generally pleased with my food; Food 3: My life in relation to food and meals is close to ideal; Food 4: With regards to food, the conditions of my life are excellent; Food 5: Food and meals give me satisfaction in daily life.). In each scale, the respondents must indicate their degree of agreement with these statements using a 5-level Likert scale (1 = disagree completely, 5 = agree completely). Each item will be calculated and reported separately and totally [39].

A picture of the participants’ refrigerator will be used to assess the qualitative and quantitative contents of refrigerators (at *t* = 0, *t* = 2). The categories will be “sufficient”, “in-sufficient” (e.g. with old food, according to date or appearance) or “empty” (less than 3 solid food) [40, 41].

For each participant sociodemographic data will be collected; this include age, marital status and yes/no if living alone (at t = 0). Also, data describing numbers of meals delivered by meals-on-wheels on a weekly basis will be collected.

Compliance i.e. use of and participation in possible and suggested activities in relation to meals, number of visits from Dieticians and other staffs involved, plus reasons for canceling of such planned visits and unintended adverse events/possible problems related to the suggested intervention strategies will be recorded during the 8 weeks of intervention period.

After each contact (visit or telephone) with participant following information will be registered by the Case Manager/RD:who were present at the meeting if the contact was a visit,which interdisciplinary contact within the municipality was made afterwards,the time spent on the specific contact,the Case Managers/RD’s judgment (yes/no) if the participants were motivated in the collaboration, andany unintended adverse events/possible problems related to the suggested intervention.

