#### Blinding

An RA from the manager group in The City of Odense performing the allocation of clusters has no contact with the community aged care groups and will be blinded from all aspects of allocation and subsequent intervention. Participants, Care Managers/RD’s, the principal investigator ([name]) and RA’s ([name]) will not be blinded for the intervention. Data will be analyzed by an external RA, who will be blinded for the results of randomization.

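### The refrigerator categories mix a quality criterion with a quantity criterion, so one picture can fit two labels, and nothing provides for masked grading of the photograph

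*Protocol article*

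**What the plan says.** The Secondary outcomes section uses a picture taken at baseline and follow-up "to assess the qualitative and quantitative contents of refrigerators". The result is one variable with three levels: *sufficient*, *in-sufficient* and *empty*. The last two are worded as "in-sufficient” (e.g. with old food, according to date or appearance) or “empty” (less than 3 solid food": *in-sufficient* is explained by an example, and *empty* by a count. Table 1 repeats the three labels and adds no rule. Two references are cited for the measure.

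The Outcomes section has the assessments made in the home by research assistants and Case Managers. It says they are not made by the same person at each time point, that all assessors receive the same training, and that "Due to the design of the study it is not possible to blind neither the RA’s nor the Case Managers/RD’s". The Blinding section adds: "Data will be analyzed by an external RA, who will be blinded for the results of randomization".

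On meal supply, the Intervention section describes usual care as one to seven meals a week, "hot meals-on-wheels arriving one to three times per week".

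**The concern.** A three-level outcome needs each picture to fall into one level only. Here one level rests on the condition of the food and another on how much there is, and both can be true of the same refrigerator. The assessor must then choose, and the article gives no rule for choosing.

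Three features of this trial make that choice matter more:

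- The assessors differ between visits and know the allocation. Some of them deliver the intervention.
- The Implementation section recruits the intervention cluster first and the control cluster afterwards. A drift in grading habits over time could therefore line up with arm.
- The pilot exists to test the outcome measurements, but the Primary outcome section judges feasibility by the ratio of completed to non-completed measurements. A picture that was taken would presumably count as complete even if two graders would label it differently. The pilot's own test would not show the problem, and the definition could pass unchanged into the definitive trial.

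**Working it through.** The article attaches no rate, power or error figure to this outcome, so there is nothing to reproduce. Two checks were made.

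**Check 1: are the categories exclusive?** Cross the two stated criteria.

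| Solid items | Old food present? | Label that the wording supports |
|---|---|---|
| Fewer than 3 | No | *empty* |
| 1 or 2 | Yes, among them | *empty* by count and *in-sufficient* by example |
| 3 or more | Yes | *in-sufficient* by example; how much old food is needed is not said |
| 3 or more | No | presumably *sufficient*, by default |

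The second row is the defect: two labels apply and neither is given precedence. This follows from the wording alone and needs no assumption.

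**Check 2: could the visit day change the label?**

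Inputs from the article: one to seven meals a week, one to three deliveries a week, threshold of 3 solid items.

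Assumptions that are not in the article: delivered meals are kept in the refrigerator, each counts as one solid item, one is eaten per day, the picture is taken before that day's meal, and *b* other solid items are always present.

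Let p be the share of the 7 days on which the count is below 3. Two independently chosen visit days disagree on *empty* with probability 2p(1 − p).

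| Meals and deliveries per week | b | Daily counts | Days below 3 | 2p(1 − p) |
|---|---|---|---|---|
| 7 in one | 0 | 7,6,5,4,3,2,1 | 2 | 2 × 2/7 × 5/7 = 0.41 |
| 7 in two (4+3) | 0 | 4,3,2,1,3,2,1 | 4 | 2 × 4/7 × 3/7 = 0.49 |
| 7 in three (3+2+2) | 0 | 3,2,1,2,1,2,1 | 6 | 2 × 6/7 × 1/7 = 0.24 |
| 4 in one | 1 | 5,4,3,2,1,1,1 | 4 | 0.49 |
| 4 in one | 2 | 6,5,4,3,2,2,2 | 3 | 0.49 |
| 7 in one, two or three | 2 | never below 3 | 0 | 0 |
| 1 in one | 0 | 1,0,0,0,0,0,0 | 7 | 0 |
| Any schedule tried | 3 | never below 3 | 0 | 0 |

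The range is 0 to 0.49. The upper end is also the largest value possible when p is a whole number of sevenths (24/49). The effect disappears once three other solid items are always present.

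**The case against.** Several objections carry weight.

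**Condensed article.** Grading rules, picture timing and the grader's identity are details that a full protocol or assessor manual may hold, and the cited sources may define the categories further. This stands for timing and for the grader. It does not remove the overlap, because the article itself states the two criteria and they collide as stated.

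**Common training.** All assessors are trained alike. That helps consistency, but the article describes no rule for a picture that meets both criteria.

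**Mixing quality and quantity is deliberate.** The measure is meant to cover both, so old food may properly count against a well-stocked refrigerator. This stands. A reader might infer that any single expired item makes a full refrigerator *in-sufficient*. The wording gives old food only as an example and does not say that.

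**Unblinded grading is not stated.** A reader might infer that the article fixes unblinded grading. It places this measure among the assessments made by unblinded staff, but it does not say who grades the picture. The sentence on blinding is reasonable for home visits and is not contradicted elsewhere. What remains is that masked grading is available and not provided for.

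**The delivery cycle.** A reader might infer that the intervention changes the delivery cycle and so shifts this outcome artificially. The documents do not support that. The rehabilitation tool lists, as one focus, "increase cooking abilities (e.g. semi-prepared meals-on-wheels, assistance to cook at home", but only as examples. Goals are individual and at most three, and no section says that delivery days or frequency change. Shopping and cooking are targets of the programme, so some change in refrigerator stock is an intended effect. A visit day unrelated to arm adds noise, not bias.

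**Conclusion.** The point holds for the category definitions. As worded, *in-sufficient* and *empty* are not mutually exclusive, and a refrigerator with one or two solid items, any of them old, fits both. The article gives no data on how many pictures this would affect, so the size cannot be stated. That the grade may depend on the assessor follows from the overlap together with different, unblinded assessors, on the assumption that those assessors also grade the picture.

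The visit-day effect is conditional and secondary. It needs delivered meals to be refrigerated and counted, and few other items to be present; disagreement then ranges from 0 to about 0.49.

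The consequence is limited. This is one secondary outcome in a pilot, and the sample size does not rest on it. It is worth correcting because it is cheap and because the pilot is meant to settle which measures go forward.

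**What to change.** 1. **Score two items separately**: fewer than 3 solid items (yes/no) and old or spoiled food present (yes/no). Any three-level summary can be derived from the pair. If one variable is kept, state a precedence rule under which old food leads to *in-sufficient*, in line with the article's own example.
2. **Grade masked.** Have the blinded external research assistant already named for the analysis grade the de-identified photographs in random order, with arm and visit hidden. Masking may be imperfect where the contents hint at the arm, but it removes knowledge of the participant and the visit.
3. **Optional: record days since the last meal delivery** at baseline and follow-up, so that the visit day can be examined. Table 1 marks meals-on-wheels frequency at baseline only.

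Two tempting rules should be avoided. Counting only in-date items would turn a refrigerator full of spoiled food into *empty*, against the article's own example. Leaving delivered meals out of the count would mark down a control participant who lives on them relative to an intervention participant who cooks the same amount, which builds in a difference between arms.

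The cost is a change of wording, a few hours of grading as an added task for an existing role, and one extra field.

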Three systematic reviews have looked at benefits achieved by means of meals-on-wheels offered to older adults [13–15]. Home-delivered meal programs improve diet quality and increase nutrient intakes among participants [13]. However, more research is needed to evaluate the efficacy and effectiveness of home-delivered meals for older adults on multiple outcomes [14]. Very few randomized controlled studies have assessed the beneficial effect of meals-on-wheels as a supportive intervention [15]. In addition, no randomized controlled intervention studies have been investigating rehabilitation related to limitations of “Activities of daily living” (ADL) e.g. cooking, has any beneficial effect [16].

Support at home such as meals-on-wheels means becoming accustomed to a new mealtime experience. E.g. when still able to cook older adults often hold some control over the foods that are prepared and which they eat, and which helps to foster identity. Foods prepared at home are familiar to the person, holding memories of the past and as well, the activities of grocery shopping, meal planning, and food preparation may help to preserve social, cognitive, and functional abilities.

In this pilot trial, the primary research aim is to explore the community-dwelling older adults acceptability and feasibility of the outcome measurements as methods to measure efficacy of the intervention, and to provide data to estimate the required sample size for a future cluster randomized study of community-dwelling older adults being involved in their own meals in a rehabilitation program.

The second aim of this study is to perform a pilot cluster randomized trial to understand, on an individual level, whether community-dwelling older adults receiving meals-on-wheels experience an improvement in health-related quality of life and muscle strength, being involved in their own meals in a rehabilitation program compared to usual community aged care including receiving meals-on-wheels.

The cluster design is chosen primarily to avoid contamination, since the assigned Health Care Staff and Registered Dieticians receiving additional training could not be expected to treat individual residents differently; respectively the intervention and the control group, by preference of the older person. Also, the cluster design is chosen due to practical reasons, in order not to conflict with other nutritional projects and initiatives in the participating municipality.

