The first part, will consist of education of Health Care Staff in the intervention cluster starts immediately after finishing the baseline assessments and consists of a total of one day of education divided into three days, focusing of aspects of food, meals and nutrition to older adults. The education is performed by Bachelor’s Degree Nutritional and Health Educated Professionals that work within The City of Odense. Also included in the first part of the intervention, training of the Care Manager/RDs including learning to use the new developed tool was performed. The Case Managers will be Registered Dieticians (RDs) and will before commencement of the intervention be trained in managing a rehabilitation program focusing on meals. The training will consist of three days. One day as follow-up on the rehabilitation program. Specific topics include; assessment of functional abilities in relation to meals; goal setting by means of Goal Attainment Scaling (GAS) [24], ethical considerations and communication. The training program is developed specifically for the present study in co-operation with teachers from The University of Southern Denmark (SDU) - Master in Rehabilitation.

The effect of the education and training is assessed due to outcomes on an individual level (see below).Second part of the intervention - Rehabilitation program

In the second part of the intervention, the individual participants in the intervention cluster, will be participating in a rehabilitation program involving collaborative goal setting with a Case Manager.

Before contacting the individual participant, the Case Manager/RD will make a review of the participant’s journal in the municipalities system to find out 1) what kind of food from the meals-on-wheels is delivered, 2) if the participant presently is involved in other rehabilitation programs within the municipality, 3) the present health care situation of the participant, and 4) if the participant formerly had any visit from a RD in the municipality. These data will only be used for the rehabilitation program by the Case Manager/RD that is visiting the participant and will not be systematic collected and registered.

The *assessment* will help the participant and the Case Manager/RD to make collaborative evidence-based *goalsetting* to select initial areas for chance of meal activities.

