### Strengths and limitations of the study

The rehabilitation approach is a new area of research in the population of community-dwelling older adults and to our knowledge, there have only been performed a few randomized controlled studies of nutritional support among community-dwelling older adults receiving support at home, using involvement in activities related to meals. This study provides an opportunity to develop and refine consistent practices of older adults’ involvement in activities in relation to meals in the communities as part of rehabilitation programs.

A clear strength of this study is the workshop in the early stage of the project, which illuminated rehabilitation due to experts, collaborators e.g. Likewise, we also consider it a strength that also representatives of the older adults in Denmark participated in this work.

In designing the study, we will choose to develop a new tool to be used in the for the rehabilitation process, but instead we could have chosen to use an already validated tool for the rehabilitation process. However, we want to make sure that the main focus of the dialog is involvement in meal related activities, and we did not find any suitable tool for this purpose.

A limitation of this study is the exclusion of severe dementia, brain injury and mental illness and this could possible reduce the representativeness of our findings. This decision is made because of the nature of the rehabilitation program including involvement in meals.

Since this study do not have much funding attached we had to make some choices in designing this study. For instance, it could have been interesting to evaluate if there would be any change in the participants community care services, use of medicine, and health challenges, since this could be an expression of the effectiveness of the intervention, however due to limitations of time and access to this information this will not be included.

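### Adverse-event recording is described only around the intervention programme and not for controls, so event rates cannot be compared between arms

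*Protocol article*

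**What the plan says.** The protocol article mentions adverse events in two places, both under Secondary outcomes.

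- In the sentence on compliance, next to uptake of activities and visit counts: "unintended adverse events/possible problems related to the suggested intervention strategies will be recorded during the 8 weeks of intervention period". This sentence names no recorder and no arm.
- In the contact log that follows: "After each contact (visit or telephone) with participant following information will be registered by the Case Manager/RD". The last item of that log is adverse events or problems, again tied to the suggested intervention.

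The programme belongs to one arm. Under Preparation of the intervention, "the individual participants in the intervention cluster, will be participating in a rehabilitation program involving collaborative goal setting with a Case Manager", and the programme "will consist of a minimum of three contacts to the Case Manager/RD". For the other arm, "The participants in the control group will receive usual care in relation to meals".

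Both arms are assessed at home. The Outcomes section says that assessments "will occur at inclusion (Baseline, *t* = 0) and at the end of the intervention period (Follow-up, *t* = 2"; the intervention cluster alone has some measures at t = 1. Table 1 has no adverse-event row. The Outcomes and Blinding sections state that neither the Research Assistants nor the Case Managers/RDs are blinded.

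**The concern.** A harm comparison needs the same question, asked in the same way, in both arms. Here the wording ties events to an intervention that controls do not receive, and the one named recorder is a person whom controls do not meet. An event count from this trial would come from one arm and have no comparator.

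The Secondary outcomes section describes the participants as old, frail and chronically ill, so untoward events can be expected whatever the allocation. The programme encourages shopping, cooking and eating independently. The results are meant to shape a definitive trial (Conclusions), which would want to know whether event rates differ. One indirect route is closed as well. On changes in care services, medicine use and health challenges, the Strengths and limitations section says: "however due to limitations of time and access to this information this will not be included".

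Within the intervention arm, the named recorder also sets the goals with the participant. If that person's view of relatedness decides what is written down, an event not linked to the programme may go unrecorded.

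**Working it through.** The plan states no safety figure, so there is none to reproduce. The check is a comparison of the text by arm.

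| Element | Intervention arm | Control arm |
|---|---|---|
| Suggested activities to which an event could be related | Yes | None; usual care |
| Named event recorder | Case Manager/RD, after each visit or call | None named |
| Programme contacts per participant | At least 3 | 0 described |
| Event item in Table 1 | None | None |
| Home assessment at t = 0 and t = 2 | Yes | Yes |

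1. *Recorder and timing.* The contact log is the only place that says who records events and when. It can operate only where there are Case Manager contacts: at least 3 per intervention participant, against 0 described per control participant.
2. *Wording.* Both statements refer to the suggested intervention. In the control arm that phrase has nothing to attach to.
3. *Table 1.* It lists 12 measures, of which 12 are taken at baseline, 6 at the in-between point and 10 at follow-up. None is an event item.
4. *Window.* Recording is described for eight weeks, which is the length given for the rehabilitation programme. Staff education comes between baseline and the programme, so the stated window does not clearly cover that interval.
5. *Result.* Followed as written, the plan gives adverse-event data for the intervention arm only, and not clearly all events there.

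**What a common question at t = 2 could deliver.** This measures the precision of the remedy, not the size of the defect. Inputs: 65 per arm (130/2, assuming an equal split) or the 53 per group stated under Sample size. The event proportion p is an assumption, because the document gives none. Half-width of the 95% interval for the difference between arms, ignoring clustering: 1.96 × √(2p(1 − p)/n).

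| Assumed p in each arm | n = 65 | n = 53 |
|---|---|---|
| 5% | ±7.5 points | ±8.3 points |
| 10% | ±10.3 points | ±11.4 points |
| 20% | ±13.8 points | ±15.2 points |

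For example, with p = 10% and n = 65: 1.96 × √(0.18/65) = 1.96 × 0.0526 = 0.103. Any correlation within the five care areas would widen these intervals.

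**The case against.** The case on the other side has real force.

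- *Exclusivity is inferred.* A reader might infer that events are recorded only at programme contacts, and only when the Case Manager judges them related. The compliance sentence supports neither: it names no recorder and speaks of recording throughout the eight weeks. The relatedness phrase may also qualify only the possible problems and not the adverse events. No adjudication rule is set out. This stands, so missed events in the intervention arm are a possibility and not a certainty.
- *Controls do yield some harm information.* EQ-5D-3L, weight/BMI, chair stand and well-being are measured in both arms at t = 0 and t = 2. This stands: it would be wrong to say that controls give no harm data. But these measures show average change, count no events, and are missing for anyone who cannot be visited at t = 2.
- *No aim fails.* The primary aim is to "explore the community-dwelling older adults acceptability and feasibility of the outcome measurements as methods to measure efficacy of the intervention", with sample-size data for a later trial; the second aim concerns quality of life and muscle strength. No safety comparison is planned. This stands too. A misleading table of some events against zero is a risk if the counts were set side by side, but the article plans no such table.
- *An article condenses.* Table 1 also leaves out compliance and visit counts, which the text says are recorded, so the missing row is not proof by itself. A fuller protocol may say more. The point nevertheless rests on what the article does state: the scope of recording, the recorder and the timing.

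**Conclusion.** The point holds as a weakness of ascertainment. As described, adverse-event recording is tied to the suggested intervention, the only named recorder is the unblinded Case Manager/RD after programme contacts, and controls have no equivalent. Adverse-event rates therefore cannot be compared between arms, and events not linked to the programme may be missed in the intervention arm.

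The size is structural: at least three described recording opportunities per intervention participant against none per control participant. How many events would be lost cannot be estimated from the document.

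A reader might go further and conclude that the pilot fails a safety objective or has no harm data at all for controls. The article supports neither conclusion. The verdict assumes that any fuller protocol does not already provide event recording for controls; if it does, the article needs only a sentence saying so. A change is worth making because it is cheap, not because the trial's aims depend on it.

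**What to change.** Amend Outcomes, Secondary outcomes and Table 1 as follows.

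- At the existing t = 2 home visit, ask every participant in both arms, in identical words, about falls, hospital admissions and other untoward events since baseline, regardless of presumed cause. Whichever assessor makes the visit asks the questions.
- Where the visit cannot be held, record the reason, including death or admission, as learned when arranging it. No record review is required, so the stated limit on access to information is respected.
- Keep the Case Manager's relatedness judgement as a separate field.
- Report all-cause events by arm descriptively. List contact-log events for the intervention arm only, and not as a comparison.

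The cost is a slightly longer visit and one descriptive table; no visit is added. Recall error and unblinded assessors remain, reasons for missed visits may be incomplete, and event rates will be estimated only imprecisely.
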